##### Concealment mechanism {16b}

Computer-generated randomisation will ensure concealed group allocation.

##### Implementation {16c}

An investigator not involved with recruitment and the screening process will set up a randomisation schedule. Additionally, assessors conducting the statistical analyses will be blinded to group allocation.

### Assignment of interventions: blinding

#### Who will be blinded {17a}

The investigators setting up a randomisation schedule on REDCap and conducting statistical analysis will be blinded to participant identities. Trial participants will not be blinded to the intervention.

#### Procedure for unblinding if needed {17b}

Not applicable, participants will be aware of the group that they have been allocated to.

### Data collection and management

#### Plans for assessment and collection of outcomes {18a}

Data will be collected through REDCap surveys and via videoconferencing for one-on-one interviews. Email notifications from REDCap will invite participants to access questions at the appropriate time points. Data will be collected through REDCap [33] (or via phone call if the participant prefers) and a computer software called Inquisit 6.

#### Primary outcome

##### Psychological distress

The K10 provides a score indicating one’s self-reported psychological distress [36]. Five possible responses are provided as answers, with corresponding numerical values. Total scores range between 10 (no distress) and 50 (severe distress). The K10 has excellent psychometric properties, including high internal consistency (Cronbach’s alpha 0.93 [36] and discriminant validity [37]).

#### Secondary outcomes

##### Physical activity

The Incidental and Planned Exercise Questionnaire (IPEQ) has been designed specifically for older people and comprises 10 items that prompt users to self-report the frequency and duration of planned and incidental physical activities. This questionnaire has excellent psychometric properties [38]. The results provide minutes across different categories of incidental and planned activities, e.g. sport, walking.

##### Social capital

The Brief Social Resources Questionnaire ([name], Registered Psychologist & UNSW School of Psychology PhD Candidate: Brief Social Resources Questionnaire 2021, unpublished) summarises the participants’ self-reported responses to questions about the context of their social capital, in particular, the objective and subjective aspects of their social resources. Three social network questions—adapted from the Lubben Social Network Scale-6 [39]—reveal a more objective and quantitative measure of their interactions, while the three questions surrounding social support—adapted from Duke Social Support Index-10 [40]—focus on the qualitative, perceived impact of those interactions. Adaptations of existing questionnaires were made to capture both objective and subjective aspects of social capital with brevity. Responses to each of the six items are standardised.

##### Cognition

Multiple aspects will be assessed through a battery of ‘brain games’ ([name], Registered Psychologist & UNSW School of Psychology PhD Candidate: Brain Games 2021, unpublished) delivered through the Inquisit 6 web application [41]. Four tasks will evaluate decision-making related to risk-taking and uncertainty (Iowa Gambling Task) [42], working memory (n-Back task) [43], cognitive flexibility (Trail-making test) [44] and emotional intelligence (EI) (Trait Emotional Intelligence Questionnaire (TEIQue)) [45]. Each task has demonstrated adequate reliability and validity for measuring each aspect of cognition.

##### Concern about falling

The Iconographical Falls Self-Efficacy Scale (Icon-FES) is used to evaluate concerns about falling. The Icon-FES is a 30-item questionnaire that uses pictures as well as words to ask about concerns about falling doing 30 common daily activities. This scale has high internal consistency and excellent test-retest reliability [46].

##### Loneliness

Loneliness and social isolation is evaluated through the 20 questions of the University of California, Los Angeles (UCLA) Loneliness Scale [47]. Questions are answered on a 4-point Likert scale ranging from ‘never’ to ‘often’. A total score over 25 represents a high level of loneliness and 30 or higher indicates a very high level of loneliness. This scale has been deemed reliable and valid when assessing loneliness in a population over 65 years [47].

##### Quality of life

The European Quality of Life Five Dimensions (EQ-5D-5L) gauges details about an individual’s mobility, self-care, usual activities like work, study, housework and leisure activities, pain and/or discomfort and anxiety and/or depression. Each dimension is scored based on one item. The tool also includes a visual analogue scale (VAS) that users rate their health status ranging from 0 (worst possible health status) to 100 (best possible health status) [48]. The EQ-5D-5L has excellent psychometric properties for a broad range of populations and conditions [49].

##### Physical functioning

The functional component of the Late Life Function and Disability Instrument (LLFDI) is used [50]. Thirty-two items are investigated on a 5-point Likert scale where individual’s answer can range from ‘never’ to ‘often’. Lower scores reflect less trouble performing physical, functional tasks. Evidence suggests that the use of the LLFDI for community-dwelling older adults can assess functional limitations is valid with the high test-retest functional component [51].

##### Enjoyment

The Physical Activity Enjoyment Scale (PACES) comprises 18 questions that are intended to be answered on a 7-point bipolar rating scale [52]. The use of this tool has been validated in older adults [53].

#### Monitoring

Participant adherence to balance exercise training will be recorded. Average weekly training duration and total training duration will be recorded through automatic data transfer to a server [17]. The intensity of challenge is monitored using a self-report modified rate of perceived exertion scale to allow exercises to be adjusted with performance changes [17].

Other data to be collected includes the number of participants who viewed each educational Facebook post and the adherence to individualised aerobic and strength programmes. This will be assessed using a survey at the post-intervention assessment point asking participants the average frequency and duration of individualised programme completion per week.

#### Interviews

Participants will also be invited to participate in a 20–30-min one-on-one semi-structured interview via Zoom. The aim will be to gain practical feedback about how the programme can be improved. Feedback will then be applied when facilitators run the programme for the waitlist control group. Participants will be asked about their experience participating in the programme and what they perceived to be the programme’s strengths and weaknesses. Of those indicating interest in this optional interview, those with both the lowest and highest adherence to the programme will be interviewed first until data saturation is achieved [54]. This is to ensure a representative sample of participants is included. Interview transcripts will be used for thematic, qualitative analysis [55].

Bias will be reduced with the use of a control group and random group allocation. This will allow a causal effect to be established for the accurate evaluation of primary and secondary outcome measures.

#### Plans to promote participant retention and complete follow-up {18b}

At data collection points, participants will receive an email invitation from REDCap to complete questionnaires. In the absence of a response, participants will receive a follow-up reminder.

#### Data management {19}

Data will be stored on the secure UNSW OneDrive and will be kept for 15 years after publication. A full data management plan can be found on UNSW’s ResToolKit, Research Data Management Plan ID H0241934.

#### Confidentiality {27}

Information about participants will be stored in a re-identifiable format where any identifiers such as name, address and date of birth will be replaced with a unique code. Only the listed researchers will have access to participant data.

#### Plans for collection, laboratory evaluation and storage of biological specimens for genetic or molecular analysis in this trial/future use {33}

Not applicable, no samples will be collected.

## Statistical methods

### Statistical methods for primary and secondary outcomes {20a}

Data analysis using IBM SPSS 25 will evaluate whether there are any significant changes between baseline and post-intervention on psychological distress and secondary outcomes, as well as between baseline and results at the follow-up point. Linear mixed models will be applied for each outcome measure, excluding physical activity, conducted using the MIXED procedure (considering data at all time points). A generalised linear mixed model with appropriate distribution will be used to analyse physical activity, measured by the IPEQ. Time will be considered a categorical variable for each outcome. Effect sizes (Cohen’s *d* and the 95% confidence intervals) will be calculated to determine the size of the within-group change between before and after treatment and between before treatment and 1-month post-intervention. Time, group and the interaction between these will be used as predictors. Marginal means drawn from the mixed models will be used.

Analyses will use all available data as per an intention-to-treat approach. The between-group difference at post-intervention and follow-up from baseline [mean difference (MD) and 95% confidence interval] will be calculated for all outcome measures using a baseline-adjusted mixed model with group as the independent variable, post-programme (week 10) and also follow-up (week 14) score on the outcome measures as the dependent variables, baseline score on the outcome measure as a covariate, and statistical significance set at *P* < 0.05. The results and effects will be reported as unadjusted and adjusted for sex and age. Time, group and the interaction between these will be used as predictors.

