### Outcomes {12}

The primary outcome is psychological distress, and secondary outcomes include physical activity levels, social capital, cognition, concern about falling, loneliness, quality of life, physical functioning and exercise enjoyment. Participants will complete all questionnaires at baseline, week 11 (post-intervention) and at the 1-month follow-up point (see Table 3) so that change from baseline to post-intervention and change from baseline to the follow-up point can be evaluated. It will take approximately 45 min for participants to complete questionnaires at each time point. A demographics questionnaire will also be completed by participants at baseline only. This will ask participants about their age, the highest level of education completed, marital status, living situation, employment status, known medical conditions, their mobility around the house and outdoors, fall history, self-reported concern about falling and Facebook usage.

**Table 3 Tab3:** Timeline for data collection

	Pre-programme		Programme	Post-programme	
	Enrolment (< − 1 week)	Baseline (− 1 week)	Weeks 1–10	End of week 10	Follow-up (+ 4 weeks)

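### The K10 treatment effect is tested at two time points, each at an uncorrected 0.05, and no result is named as deciding; if either can count, the false-positive rate is about 9% to 11%

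*Protocol article*

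**What the plan says.** The Outcomes section (12) makes psychological distress primary without attaching a time point. It has every questionnaire repeated after the programme and one month later, "so that change from baseline to post-intervention and change from baseline to the follow-up point can be evaluated". The two changes stand on equal terms.

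The statistical methods section (20a) has two paragraphs. The first describes mixed models on data from all time points, with time, group and their interaction as predictors. It speaks of significant changes from baseline and of within-group effect sizes. The second deals with the treatment comparison. "The between-group difference at post-intervention and follow-up from baseline", given as a mean difference with its confidence interval, "will be calculated for all outcome measures using a baseline-adjusted mixed model with group as the independent variable", with "post-programme (week 10) and also follow-up (week 14) score on the outcome measures as the dependent variables" and "baseline score on the outcome measure as a covariate, and statistical significance set at *P* < 0.05". It then adds: "The results and effects will be reported as unadjusted and adjusted for sex and age".

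The Sample size section (14) bases the variance on a mixed model of all three K10 measurements. It requires 68 participants for 80% power with SD 6.41 and correlation 0.6, and recruits 80. It does not say which contrast was powered. No section gives a hierarchy, a gatekeeping rule or a correction.

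**The concern.** A superiority trial with one primary outcome needs one rule for deciding whether it succeeded. Here the comparison is made on the primary outcome at two time points against the same uncorrected threshold, and each result comes in two covariate versions. A report could therefore rest its main claim on whichever result is significant without departing from the published plan. The nominal 5% would then not describe the risk of a false claim. Naming the test in advance matters more than usual in this trial because participants know their allocation and the K10 is self-reported.

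The same gap affects power. Since no contrast is named, the stated 80% cannot be attached to any particular test.

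**Working it through.** **Inputs from the protocol.** Threshold 0.05 (taken as two-sided; the protocol does not say). Two time points after baseline. Two covariate versions. Correlation between repeated K10 scores ρ = 0.6. 68 evaluable participants, 34 per arm at 1:1. **Assumptions.** Compound symmetry, complete data, and sex and age explaining either 0% or 20% of K10 variance.

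**1. The protocol's own figure.** 68 / (1 − 0.15) = 80, which agrees. The 68 cannot be checked, because the moderate effect has no number and the contrast is not stated.

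**2. Correlation between the two tests.** After adjustment for baseline, each follow-up score has residual variance 1 − ρ² = 1 − 0.36 = 0.64. The residual covariance between the two is ρ − ρ² = 0.6 − 0.36 = 0.24. The correlation between the two test statistics is 0.24 / 0.64 = 0.375.

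**3. Two time points, one model, one covariate version.** For independent tests, 1 − 0.95² = 9.75%. For bivariate normal statistics with correlation 0.375, P(at least one |Z| > 1.96) = 1 − 0.906 = 9.4%. Simulation under the null (20,000 trials per scenario, N = 68 and 80, ρ = 0.6) gives about 9.2% to 9.6%.

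**4. Wider families, same simulations.** Chance of at least one P < 0.05:

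| Results allowed to count | False-positive rate |
|---|---|
| One time point, one model, one covariate version | 5% |
| One time point, both covariate versions | 5.7% to 6.2% |
| Both time points, one covariate version | 9.2% to 9.6% |
| Both time points, both covariate versions | 10.8% to 11.5% |
| As above, plus group × time contrasts of the all-time-point model | 14.0% to 14.4% |

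The second time point causes most of the inflation. The last row depends on a reading of the first paragraph that is taken up under the objection. With ρ at 0.4 or 0.8 instead of 0.6 (N = 68), the fourth row runs from about 10.5% to 11.9% and the last from 12.8% to 15.3%.

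**5. Power of the candidate single tests.** Assume a standardised effect d = 0.5, since the protocol gives no value, with ρ = 0.6 and 34 per arm.

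- *One time point, baseline-adjusted.* Residual SD = √0.64 = 0.80. Noncentrality = (0.5 / 0.80) × √(34/2) = 0.625 × 4.123 = 2.58. Power is about 72% (t-test, 65 df). By normal approximation, 82 evaluable participants would be needed for 80%.
- *Mean of both follow-ups, baseline-adjusted.* Variance of the mean = (1 + 0.6)/2 = 0.80; subtracting ρ² leaves 0.80 − 0.36 = 0.44. Residual SD = 0.663. Noncentrality = (0.5 / 0.663) × 4.123 = 3.11. Power is about 86%. By normal approximation, 56 evaluable participants would be enough for 80%.

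**The case against.** The strongest reply is that no sentence says a significant result at either time point makes the trial positive. The protocol reports two estimates under a conventional threshold, and an analysis plan that is not shown may say which one leads. The model with a group × time interaction, together with a sample size built on three time points, also allows another reading: one overall interaction test at 5%. Showing results with and without covariates is ordinary practice and need not mean two routes to success.

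Much of this stands. The either-result rule is an inference, so the rates above are what follows if it is applied; the protocol does not commit to it. The covariate versions add only about 1.5 to 2 percentage points. But the interaction test is nowhere said to decide or gate anything. Nor does the point rest on silence alone: the article fixes two time points under one uncorrected threshold on the primary outcome.

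A reader might go further and infer that the treatment effect is tested under two competing models, each at 0.05, for a rate of about 14%. The same reader might object that the change contrast has 25% more variance than the baseline-adjusted one (0.80 / 0.64 = 1.25). The text does not support this firmly. It assigns the between-group difference to the baseline-adjusted model and puts the threshold in that same sentence. The first paragraph mainly serves changes from baseline and within-group effect sizes. The abstract's statement that mixed models determine the between-group differences fits the baseline-adjusted model equally well. The interaction term keeps the wider reading possible, but no sentence calls it a second test of treatment effect.

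**Conclusion.** The point holds in this form: the between-group K10 difference is tested at post-intervention and at follow-up, each at an uncorrected 0.05 and in two covariate versions, and nothing says which result decides. If either time point may count, the false-positive rate is about 9%. If either covariate version may count too, it is about 11%. These figures assume two-sided tests, complete data, compound symmetry with correlation 0.6, and a modest or null effect of sex and age. The figure near 14% is conditional on the wider reading of the first model and should not be quoted as the plan's error rate. The defect is an unspecified decision rule on the primary outcome; it should be repaired before the unblinded analysis.

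**What to change.** Before any unblinded analysis, add a dated statement naming one confirmatory K10 contrast from the baseline-adjusted mixed model, with the covariate set (with or without sex and age) fixed. The protocol does not favour one choice over another. Any of these would do:

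- the post-intervention difference, with follow-up tested only if that is significant;
- one test on the mean of both follow-ups;
- both time points kept, with a multiplicity correction such as 0.025 each, which holds the overall rate to at most 5%.

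Label the other covariate version and the all-time-point model as sensitivity or descriptive, and tie the stated 80% power to the contrast chosen.

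The text change is a few sentences and needs no new data. Trial status reports data collection complete, so the statement carries weight only if it clearly predates unblinding. There are real costs. Under the first option, an effect seen only at follow-up can no longer count as primary success. A single time point also falls short of the stated power at d = 0.5 (about 72%). The mean of both follow-ups does better (about 86%), but that calculation assumes the same effect at both times, and an effect present at only one would be diluted. Splitting the threshold lowers the power of each separate test.

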### Interim analyses {21b}

Not applicable, no interim analyses are planned.

### Methods for additional analyses (e.g. subgroup analyses) {20b}

Subgroup analyses will be conducted on psychological distress for the following groups:Those who demonstrate mild or higher levels of psychological distress at baseline, indicated by a K10 score of 20 or aboveParticipants who complied with the intervention, including those who reached a *StandingTall* training duration of at least 2 h per weekThose who experienced at least one fall in the last year versus those who had not

Effect sizes (Cohen’s *d* and the 95% confidence intervals) will be calculated to determine the size of the within-group change between before and after treatment and between before treatment and 1-month post-intervention.

### Methods in analysis to handle protocol non-adherence and any statistical methods to handle missing data {20c}

A sub-group analysis is planned to include participants who complied with the intervention, including those who reached a *StandingTall* training duration of at least 2 h per week. We will report the number of participants with missing scores for each outcome.

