**Methods:**

A randomised controlled trial with a waitlist control will be conducted, recruiting 80 adults aged 60+ years with access to Facebook and a computer or tablet and not currently meeting the aerobic physical activity guidelines. Randomisation will be completed using REDCap. The intervention group (*n* = 40) will join a private Facebook group where allied health facilitators will provide targeted healthy lifestyle education throughout the 10-week programme with weekly telehealth group calls. Intervention participants will also be provided access to tailored strength and aerobic exercise guidance and an evidence-based eHealth balance exercise programme. Psychological distress and secondary outcomes will be assessed at baseline, 11 weeks (post-intervention) and 16 weeks (1-month follow-up). Linear mixed models will be applied for each outcome measure as per an intention-to-treat approach to determine the between-group differences. Secondary analyses are planned in people with greater adherence and those with higher psychological distress.

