The *StandingTall* eHealth programme provides home-based exercise to improve balance and reduce fall risk [16]. Individuals will be provided with access to the programme and a manual on setting up and using the application. They will join a small group video call to receive assistance from a facilitator to set up the app and will be encouraged to contact the primary study investigator for assistance with any technological difficulties or queries. The app will provide participants with an individualised exercise programme that will suit their abilities, but remains challenging, based on a baseline balance assessment. This assessment will be completed in week 1 when the participants are guided to set up their *StandingTall* account. The programme will be progressed automatically based on the reported rate of perceived exertion through training. Exercises will train static and dynamic balance, stepping in different directions, functional strength and dual-task activities. Frequency, duration, intensity and dose of *StandingTall* training will be individualised to participants, but participants will be guided by facilitators to set goals around completing their exercise programmes with the aim of encouraging all to gradually complete a recommended dose of 2 h of balance training per week. Website analytics will track adherence data and time spent on the app data through individual logins.

Participants will also receive individualised support from allied health facilitators, including tailored aerobic and strength exercise programmes prescribed by Accredited Exercise Physiologists depending on participants’ health needs and activity interests. Exercise programmes will be designed to encourage participants to reach the physical activity guidelines of 150 min of moderate to vigorous activity, unless the participant indicates during goal setting that this volume is unrealistic for their abilities and/or circumstance [9].

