At the conclusion of the 10-week programme, the Facebook groups and *StandingTall* programme will remain accessible without input from facilitators. The waitlist control group will also have access after their final assessment at 14 weeks from baseline. They will join a private Facebook group (separate from the intervention group) and complete the facilitated intervention without answering additional questionnaires. Based on feedback from the intervention group, the researchers will be using the waitlist control programme to trial new features of the programme such as additional topics suggested.

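### The complier subgroup for K10 is chosen on StandingTall use that no control can have, so it loses the protection of randomisation and can show a benefit without any true effect

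*Protocol article*

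**What the plan says.** The section on non-adherence and missing data {20c} states: "A sub-group analysis is planned to include participants who complied with the intervention". It names as included those who reached a StandingTall "training duration of at least 2 h per week". The section on additional analyses {20b} repeats the rule. It introduces its list with "Subgroup analyses will be conducted on psychological distress for the following groups" and sets compliers beside two groups that can be identified at baseline in both arms: K10 of 20 or above, and a fall in the past year. The effect measure given there is Cohen's d with a 95% interval, "to determine the size of the within-group change between before and after treatment" and again to the 1-month follow-up.

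On control access, Intervention description {11a} says: "The waitlist control group will also have access after their final assessment at 14 weeks from baseline". The same section describes StandingTall use as built up over time, "with the aim of encouraging all to gradually complete a recommended dose of 2 h of balance training per week".

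The Abstract announces the analysis: "Secondary analyses are planned in people with greater adherence". The Limitations section says that the adherence and high-distress subgroups will have limited power and gives no other caution. The main analysis is described in {20a}: "Analyses will use all available data as per an intention-to-treat approach".

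**The concern.** A subgroup defined at baseline splits both arms in the same way, so a randomised comparison survives inside it. Compliance does not work like that. It arises after allocation and can be observed only in the intervention arm. The controls who would have complied exist but cannot be identified.

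Two comparisons remain. Adherers can be set against all controls, which mixes any treatment effect with whatever makes people persist with a home exercise programme. Or adherers can be set against their own baseline, which drops the control arm altogether. Either could support a statement that the programme works in those who use it when the difference is due to selection or time. Low power is a different problem: a larger sample would cure it but would leave this bias unchanged.

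**Working it through.** **Inputs from the protocol.** Sample size {14}: SD 6.41, correlation between repeated values 0.6, n = 68 before dropout, 15% dropout, N = 80. The dropout step reproduces: 68 / (1 − 0.15) = 80. That leaves 34 analysed per arm. Significance is set at P < 0.05 in {20a}; I take it as two-sided, which is 2.5% in the direction of benefit.

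**Inputs assumed.** The share p of the intervention arm counted as adherers, and the correlation r between propensity to adhere and a better K10 course after adjusting for baseline. Neither is in the documents, so a range is shown. The true treatment effect is set to zero and K10 is treated as normal.

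**Adherers against all controls, adjusted for baseline K10.** The residual SD is 6.41 × √(1 − 0.6²) = 6.41 × 0.8 = 5.128. If adherers are the top fraction p on a normal propensity, with φ the normal density and z the cut-point, the spurious benefit is

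bias = r × [φ(z) / p] × 5.128.

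- p = 20%, r = 0.3: 0.3 × 1.400 × 5.128 = 2.15 points
- p = 60%, r = 0.2: 0.2 × 0.644 × 5.128 = 0.66 points
- r = 0, any p: 0

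A simulation of the same setting (34 per arm, 3,000 runs each, baseline-adjusted) agrees:

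| Adherers | r | Bias by formula (points) | Bias simulated (points) | False significant benefit |
|---|---|---|---|---|
| 30% | 0.2 | 1.19 | 1.22 | 9.3% |
| 30% | 0.3 | 1.78 | 1.73 | 14.3% |
| 50% | 0.2 | 0.82 | 0.81 | 6.6% |
| 50% | 0.3 | 1.23 | 1.24 | 12.4% |
| 70% | 0.2 | 0.51 | 0.47 | 4.9% |
| 70% | 0.3 | 0.76 | 0.78 | 8.1% |

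At r = 0 false benefit was 2.4-2.6%. With everyone analysed as randomised it was 1.8-3.0% in every setting, against a nominal 2.5%.

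**Adherers against their own baseline.** This is the form of comparison that {20b} states. With 50% adherers and no time trend, a paired test gave false benefit in 2.9% of runs at r = 0 and 14.5% at r = 0.3. If both arms improve by 0.3 SD (0.3 × 6.41 = 1.9 points) for reasons unrelated to treatment, the figures are 26.9% at r = 0 and 57.8% at r = 0.3. This comparison can therefore mislead even when adherence is unrelated to prognosis.

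**The 2 h criterion.** Table 2 uses week 1 for set-up and prompts use from week 2. Table 3 records both average weekly and total duration. If the criterion is a 10-week average, 120 min in each of weeks 2 to 10 gives 9 × 120 / 10 = 108 min. An illustrative build-up of 40, 80 and then 120 min from week 4 gives (40 + 80 + 7 × 120) / 10 = 96 min, or 960 / 9 = 107 min over weeks 2 to 10. All fall below 120. If the criterion is a level attained, both people qualify. The text does not say which is meant.

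**The case against.** The main analysis is intention-to-treat, which is itself the primary way of dealing with non-adherence. The Abstract calls the adherence analysis secondary, and nothing in the protocol lets it decide the trial's conclusion. This stands, and it limits the seriousness of the point.

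The size of the bias rests on assumed values, and the protocol specifies no between-arm test for compliers. This also stands. The false-benefit rates in the table apply only if such a test is run. Baseline adjustment would remove the part of the selection due to baseline distress, and the calculation already allows for that. It does not rescue the within-group measure, which the protocol does specify.

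The remaining detail could belong in an analysis plan. That is true of the exact definition of compliance, since the wording gives 2 h of StandingTall as an included criterion and need not be exhaustive. It is not true of the selection rule, the outcome or the effect measure, which the protocol fixes.

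Two stronger readings are tempting and are not supported. A reader might infer that the cut-off leaves a very small group. The documents give no expected share, and Background and rationale {6a} reports high adherence to 2 h per week in the earlier StandingTall study, although that study was longer and delivered differently. A reader might also infer that anyone following the programme must be classed as non-compliant. That follows only if the criterion is an average over all ten weeks and nobody later exceeds 2 h, and the protocol says neither.

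**Conclusion.** The concern holds for the analysis as stated. The complier subset is defined by a post-randomisation variable that exists in one arm only, and the sole caution given is about power. Against all controls, the spurious benefit is about 0.66 to 2.15 K10 points for r of 0.2-0.3 and 20-60% adherers, and nil at r = 0. The right strength is therefore that the analysis can mislead, not that it will. The within-group Cohen's d cannot separate treatment from time trend or regression to the mean, whatever the value of r. The intention-to-treat comparison is untouched. The 2 h criterion is ambiguous and needs to be reconciled with the week-2 start and the gradual build-up; a contradiction is not shown. This should be changed, but it does not threaten the primary result.

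**What to change.** 1. State that conclusions about efficacy rest on the intention-to-treat analysis.
2. Replace the complier subset, as the method for non-adherence, with a complier-average causal effect analysis: all randomised participants kept, allocation as the instrument, two-stage least squares with baseline K10 as covariate. Controls cannot reach the programme before their final assessment, so non-compliance is one-sided, which suits the method.
3. Define compliance on participation in the whole programme. With StandingTall minutes alone, the Facebook and tailored exercise components could act on K10 by another route and break the exclusion restriction. Any binary cut-off strains that assumption, because partial users may also benefit, so state it openly. Check which records exist per person: the protocol describes Facebook views as a count of viewers for each post.
4. Report K10 by StandingTall minutes within the intervention arm as descriptive only, with no efficacy claim.
5. Say whether the 2 h criterion is an average (and over which weeks) or a level attained, and reconcile it with Intervention description {11a}, Table 2 and Table 3.
6. Add selection to the Limitations alongside power.

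The cost is some analysis work, revised wording and lower precision. With 34 per arm the baseline-adjusted intention-to-treat standard error is about 5.128 × √(2/34) = 1.24 points. Dividing by the share of compliers gives roughly 1.24 / 0.6 = 2.1 points at 60% and 1.24 / 0.2 = 6.2 points at 20%. The estimate will be wide, and the report should say so.
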